**Fig. 1 Fig1:**
[figure not shown]
The flowchart of the proposed trial. MDT: metastasis-directed therapy; cRP: cytoreductive radical prostatectomy; ECOG PS: Eastern Cooperative Oncology Group Performance Status; RT: radiation therapy; ADT: androgen deprivation therapy; PSMA-PET/CT: prostate-specific membrane antigen positron emission tomography/computed tomography; PSA: prostate-specific antigen; CTCAE: Common Terminology Criteria for Adverse Events

The primary endpoint is the proportion of patients with undetectable prostate-specific antigen (PSA), no disease progression, and no symptomatic deterioration after 6 treatment cycles. Undetectable PSA is defined as ≤ 0.2 ng/mL and confirmed by two successive evaluations at least 3 weeks apart. Disease progression will be evaluated by a blinded independent central review (ICR) according to the Response Evaluation Criteria in Solid Tumours (RECIST) version 1.1. Symptomatic deterioration is referred to as a situation where the treatment needs to be interrupted, but with no apparent disease progression.

The secondary endpoints include the following:Percentage of cases with undetectable PSA after 3 treatment cycles.PSA50 and PSA90 response rate after 3 and 6 treatment cycles. PSA50 and PSA 90 response rate are the percentages of patients who have a reduction of greater than 50% and 90% from baseline, respectively.Comparisons of baseline conventional imaging and PSMA PET/CT imaging features, including tumor-node-metastasis (TNM) staging, molecular imaging TNM (miTNM) classification, number of metastases, and metastatic sites.Proportion of patients with ≤ 10 metastases (except pelvic lymph node metastases without new metastases) assessed by PSMA PET/CT at the end of cycle 3.Comparison of conventional imaging and PSMA PET/CT imaging features at the end of the 3 and 6 treatment cycles, including change in prostate volume, number and volume of prostate tumor nodules, distribution of metastatic lesions and number of metastatic lesions.Safety assessment: including adverse events (graded according to National Cancer Institute's Common Terminology Criteria for Adverse Events 5.0 criteria) and surgical complications (graded according to Clavien-Dindo classification).Assess the feasibility of implementing cRP ± MDT based on the number of metastases in PSMA PET/CT.

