### Inclusion criteria

Participants who satisfy all the following will be eligible for the study.Able to understand and willing to sign the informed consent.Men aged ≥ 18 years.With histologically or cytologically confirmed prostate adenocarcinoma (primary small cell carcinoma or signet-ring cell carcinoma of the prostate are not allowed, however adenocarcinoma with neuroendocrine differentiation accounting ≤ 10% is allowed).Newly diagnosed prostate cancer (within 3 months prior to enrollment).With distant metastatic disease (M1a/b staging) assessed via conventional imaging including bone imaging, conventional CT, or magnetic resonance imaging [MRI].With ≤ 10 distant metastatic sites assessed via conventional imaging before systemic treatment.Receipt of apalutamide plus ADT as first-line treatment is the next treatment option. Prior therapy with ADT or first-generation antiandrogen agent (e.g., bicalutamide, flutamide) or apalutamide + ADT for ≤ 2 months before enrollment are permitted.Receipt of PSMA PET/CT within 6 weeks before receiving apalutamide plus ADT and without prior treatment of NHT or chemotherapy before PSMA PET/CT examination.Willing to accept cRP and/or PLMD ± MDT.With Eastern Cooperative Oncology Group performance status of 0–1.With adequate organ function.With life expectancy ≥ 12 months.

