### Assessments

Serum PSA will be assessed, and PSMA PET/CT imaging will be performed once every 3 cycles during the systemic treatment [27]. If serum PSA level increases or patients suffer from osteodynia, chest, abdominal, and pelvic CT/MRI imaging will be performed. The participants will be followed up via telephone until the end of the study, death, or loss to follow-up, within ± 4 weeks (Table 1). ^68^Ga or ^18^F can be used as a tracer and the type of tracer for each patient will remain unchanged throughout the study.

**Table 1 Tab1:** Participant timeline

	Screening Period		Observation and Treatment Period											Group Exit Confirmation	Follow-up Period
Item	Within 14 days before first dosing	Within 7 days before first dosing	1st cycle	2nd cycle	3rd cycle		Planned surgery date (First 7 ± 1 days)	Surgery date	After surgery date (14 ± 3 days)	4th cycle	5th cycle	6th cycle	6th cycle	Group-exit investigation & observation confirmation	Safety & survival follow-up
			C1D1 (± 3 days)	C2D1 (± 3 days)	C3D1 (± 3 days)	C3D28 (± 3 days)				C4D1 (± 3 days)	C5D1 (± 3 days)	C6D1 (± 3 days)	C6D28 (± 3 days)	C6D28 + 30 (± 7 days)	Once every 3 m in 1st–2nd y; once every 6 m in 3rd y
Signing of informed consent [1]	√														
Demographic characteristics and history of tumor or other diseases [2]	√														
Vital signs [3]		√				√	√						√	√	
Physical examination [4]		√													
ECOG scoring [5]		√				√							√	√	
Testosterone examination [6]	√														√
Blood routine [7]		√													
Urine routine [8]		√													
Occult blood in stool [9]		√													
Blood biochemistry [10]		√													
Blood coagulation function [11]		√													
HIV, Hepatitis B, Hepatitis C [12]	√														
12-lead electrocardiogram [13]		√													
Ultrasonic cardiogram [14]	√														
Prostate specimen examination [15]	√							√							
PSA examination [16]		√				√							√	√	√
Imaging examination [17]	√												√		√
Bone scan [18]													√		√
PSMA-PET [19]	√					√									√
Metastasis-directed therapy [20]										√					
Systemic therapy drug compliance [21]						√							√	√	
Concomitant drug/therapy [22]	√													√	
Adverse event recording [23]						√							√	√	
Progressing event, survival state, and subsequent tumor treatment [24]														√	√

Description:

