### Statistical analysis

The primary endpoint is the rate of participants with an undetectable PSA after 6 cycles of the apalutamide plus ADT. Fleming's two-stage group sequential design will be employed in this study, where the null hypothesis is that the rate of participants with an undetectable PSA will be ≤ 40%, and the alternate hypothesis was an undetectable PSA of > 60%. The test will be one-sided, with an α of 0.05 and a power value of 0.80. The first stage of the study will enroll 21 patients; if the number of patients with undetectable PSA is ≤ 8 during this stage, this treatment strategy will be considered ineffective and the study will be terminated. In case the number of patients with undetectable PSA is > 8 at the initial stage, this study will enter its second stage, when more patients will be added to reach the sample size of 42. If the number of patients with undetectable PSA is ≤ 22 during this period, this protocol will be considered ineffective. With an assumption of a dropout rate of 10%, a total of 47 patients will be needed for the effective analysis.

The full analysis set (FAS) will be used for efficacy analysis. The FAS follows the intend-to-treat (ITT) principle, where patients receiving at least one treatment are included in the analysis. The safety analysis set will include all patients receiving at least one treatment in this study, using the safety records after the treatment.

Quantitative data with normal distribution or near normal distribution will be expressed as mean ± standard deviation; those with skewed distribution or heterogeneity of variance will be expressed as median and quartile. Categorical data will be expressed as numbers and percentages. Categorical data will be analyzed by chi-square test or Fisher's exact test. The Kaplan–Meier method will be used to calculate the median times (95% confidence intervals) for time-to-event variables and generate survival plots. Each variable will be analyzed against the baseline value of the screening period. Paired t-test, χ2-test, exact probability method, or non-parametric test will be utilized to assess the differences of determinants before and after the study.

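### PSA50/PSA90 are scored from a screening PSA that may already be on treatment, so response is understated in pretreated patients

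*Protocol article*

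**What the plan says.** Four statements in the protocol article bear on this point.

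- **Baseline rule (Statistical analysis):** "Each variable will be analyzed against the baseline value of the screening period".
- **Endpoint (Trial overview, secondary endpoints):** the list includes "PSA50 and PSA90 response rate after 3 and 6 treatment cycles", and these rates "the percentages of patients who have a reduction of greater than 50% and 90% from baseline, respectively". Baseline is not defined separately for them.
- **PSA timing (Assessments, Table 1):** the only PSA tick before treatment is in the column headed "Within 7 days before first dosing".
- **Prior therapy (Inclusion criteria):** ADT alone, a first-generation antiandrogen, or "apalutamide + ADT for ≤ 2 months before enrollment are permitted".

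On imaging, the inclusion criteria ask for "Receipt of PSMA PET/CT within 6 weeks before receiving apalutamide plus ADT and without prior treatment of NHT or chemotherapy before PSMA PET/CT examination". Table 1 ticks the baseline PSMA PET under "Within 14 days before first dosing".

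**The concern.** PSA50 and PSA90 measure how far PSA falls under treatment. A patient who has had several weeks of ADT, or of the study combination itself, reaches the screening draw with part of that fall already behind him. The stated rule discards that part and asks for a further 50% or 90% fall from the lowered value. A good responder can then be counted as a non-responder.

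The rates at stake are a named secondary endpoint at two time points. The exploratory correlation of PSMA PET measures with PSA response would carry the same misclassification. Pooled rates would mix two quantities: total decline in untreated patients and residual decline in pretreated ones. The mix would depend on how many pretreated patients happened to enrol.

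**Working it through.** **1. The plan's own design figures, and whether they are touched.** Inputs from the Statistical analysis section: stop if 8 or fewer of 21 succeed; ineffective if 22 or fewer of 42; rates 40% and 60%; dropout 10%. The chance of success at true rate p is the sum over x = 9 to 21 of P(X1 = x) × P(X2 ≥ 23 − x), with X1 and X2 each binomial(21, p).

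- At p = 0.40: 0.0367, within the one-sided 0.05.
- At p = 0.60: 0.798, against the stated 0.80.
- 42 / (1 − 0.10) = 46.7, rounded up to 47.

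The design reproduces. The PSA component of its endpoint is the absolute limit of 0.2 ng/mL, so the definition of baseline enters none of these figures.

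**2. What the rule does to PSA50/PSA90.** Let P be the pre-therapy PSA and f the fraction by which it has fallen at screening. The screening value is S = P(1 − f). A PSA90 response needs a later value below 0.1 × S, which is a total decline from P above 1 − 0.1(1 − f). For PSA50 it is above 1 − 0.5(1 − f). The values of f are assumptions; the document gives none.

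| Assumed fall before screening, f | Total decline needed for PSA90 | Total decline needed for PSA50 |
|---|---|---|
| 0% | 90% | 50% |
| 50% | 95% | 75% |
| 80% | 98% | 90% |
| 90% | 99% | 95% |
| 95% | 99.5% | 97.5% |
| 99% | 99.9% | 99.5% |

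From a pre-therapy baseline the thresholds stay at 90% and 50% in every row.

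**3. One illustrative patient (invented values).** PSA is 100 ng/mL before therapy, 5 at screening and 1 after 3 cycles.

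- From screening: (5 − 1)/5 = 80%, a PSA90 non-responder.
- From the pre-therapy value: (100 − 1)/100 = 99%, a responder.

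**4. A clash with the trial's own PSA threshold.** A patient screened at 0.4 ng/mL who falls to 0.2 reaches the undetectable limit. His decline is (0.4 − 0.2)/0.4 = 50%, which is not greater than 50%, so he fails PSA50. From 2 ng/mL, a fall to 0.2 is exactly 90% and fails PSA90.

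**5. Possible effect on the reported rate.** Assume a PSA90 rate of 90% from the pre-therapy value in all patients, a pretreated share q, and a rate r of 30% to 70% among pretreated patients when scored from screening. The reported rate is (1 − q) × 0.90 + q × r.

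| Assumed q | r = 30% | r = 70% |
|---|---|---|
| 10% | 84% | 88% |
| 25% | 75% | 85% |
| 50% | 60% | 80% |

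With q = 0 there is no effect. All three inputs are assumptions.

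**6. The PET windows side by side.** Take a patient already given apalutamide plus ADT for more than 14 days before the first on-study dose. The inclusion criterion puts his PET before that therapy began, hence more than 14 days before on-study dosing. Table 1 puts it within 14 days. Both cannot be met. A patient pretreated with ADT or a first-generation antiandrogen alone can meet both, by having the PET within 14 days before his first apalutamide dose.

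**The case against.** **First dosing may mean the first dose ever received.** The screening PSA would then precede therapy, and a 14-day PET window would fit inside the 6-week one. The article does not rule this out. But Table 1 also places consent within 14 days before first dosing, while the inclusion criteria speak of therapy given before enrolment. The first on-study dose is the natural reading.

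**The error is conservative and confined to a secondary endpoint.** This stands. Where PSA has fallen before screening, the rule lowers PSA50/PSA90 and cannot raise them. The stopping and success limits are unaffected.

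**Prior treatment is already recorded.** Note a to Table 1 collects anticancer treatment history, including hormone therapy, so pretreated patients can be identified. That makes the repair easier but does not change the stated baseline.

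**Analyses by prior therapy may be left to the analysis plan.** Their absence from an article is not a fault, and they are offered below only as part of the remedy. The fault is the rule the article does state.

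Three stronger readings might be inferred, and the document does not support them:

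- *Every change-from-baseline analysis is compromised.* The baseline PSMA PET must precede novel hormone therapy, so it cannot be on apalutamide, although it may be on ADT or a first-generation antiandrogen. The eligibility lesion count on conventional imaging is taken before systemic treatment.
- *The primary rate is biased upward against 40%.* Up to 2 months of earlier exposure may add to the treatment behind the result. The article does not say where 40% comes from or whether that population was pretreated, so bias against it cannot be asserted. The relative extra exposure is also unsettled: 60 days is 36% of 6 × 28 = 168 days, but 25% of about 240 days, the 8-month maximum for patients having cytoreduction.
- *The PET windows conflict for anyone pretreated beyond 14 days.* They conflict only for patients pretreated with apalutamide plus ADT.

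**Conclusion.** The concern holds for PSA50 and PSA90. On the article's own text, a pretreated patient's reference PSA is an on-treatment value, possibly on the study regimen, and his response is understated to the extent that PSA fell before screening. With an assumed 90% fall, the effective PSA90 bar rises from 90% to 99% and the PSA50 bar from 50% to 95%.

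The effect on the reported rates cannot be sized, because neither the share of pretreated patients nor their earlier PSA fall is given. It is nil if no pretreated patients enrol. The conclusion takes first dosing in Table 1 as the first on-study dose. The primary endpoint's PSA threshold and the two-stage design are unaffected by the choice of baseline. The PET-window conflict is real on the same reading, for the limited group described above.

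**What to change.** - **Redefine baseline PSA for PSA50/PSA90** as the last value before any ADT, antiandrogen or apalutamide, and except these endpoints from the general screening-value rule.
- **Collect that value** and its date, with the date of the first systemic dose, from source records. Diagnosis must fall within 3 months before enrolment and original medical records are kept, so it should usually be retrievable.
- **Report PSA50/PSA90 by prior systemic therapy** (none or some). Report the primary rate in the same split as a sensitivity analysis, leaving the primary test as it is.
- **Reconcile the PSMA PET window in Table 1 with the inclusion criterion**, and state what first dosing means. Which window applies is for the investigators to decide.

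The cost is a change of wording and a few case report form fields. The drawback is that some pre-therapy PSA values will be missing; their number should be reported and their handling stated in advance. Sample size and decision limits do not change.

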### Study status

The CHAMPION study commenced patient enrollment in March 2023 and is currently ongoing with patient recruitment.

## Discussion

Metastatic prostate cancer is a major cause of mortality among men [1]. The proportion of patients with advanced prostate cancer when first diagnosed and treatment is higher in China compared to other developed counties [3]. The 5-year OS rate of patients with newly diagnosed metastatic prostate cancer is only about 32.3% [5]. In metastatic prostate cancer, the oligometastatic state (low-tumor-burden disease state) differs in biological characteristics, clinical manifestations, and response to therapeutic intervention, compared to the advanced metastatic state, providing a good treatment window to prevent/slow disease progression [6, 7]. Therefore, developing effective treatment strategies for prostate cancer with oligometastatic state would be beneficial to many patients with metastatic prostate cancer.

MMT consists of local therapeutic intervention and systemic treatment and is recommended for low-volume mHSPC [17, 18]. Investigators at John Hopkins University first proposed total eradication therapy (TET) in 2019. The MMT protocol for TET comprised systematic treatment, local therapeutic intervention, and MDT, and preliminarily demonstrated the feasibility and efficacy in managing metastatic prostate cancer. The HORRAD and STAMPEDE clinical trials also confirmed the benefits of combined treatment with local therapeutic intervention and systemic treatment in mHSPC patients [21, 28]. Systematic treatment mostly included conventional ADT; currently, the NHT containing apalutamide plus ADT has become the standard treatment option for mHSPC. However, the effect of this combined therapy in patients with low-tumor-burden mHSPC still needs to be explored.

Limitations on the number of distant metastases that determines whether patients should undergo MMT or not continuously vary with changes in treatment techniques and notions. In the STAMPEDE trial, the survival benefits and failure-free survival were dependent on the number of bone metastases based on the subgroup analysis [21]. In patients with ≤ 4 bone metastases, the OS was significantly prolonged after radiation therapy; patients with 4–8 bone metastases still benefited from the radiation therapy; patients with as many as 9 bone metastatic sites benefited only from failure-free survival. Assessing SBRT in patients with 4–10 metastases, a phase III clinical study (SABR-COMET-10) found SBRT feasible and effective in patients with pan-tumor oligometastases, including 4–10 prostate cancer oligometastases [14]. This proposed trial will incorporate patients with newly diagnosed mHSPC and ≤ 10 metastatic sites to determine the feasibility and potential benefit of MMT.

Furthermore, identifying the suitable lesion and selecting the optimal timing and in MDT treatment remains controversial. Since PSMA PET/CT has higher diagnostic accuracy than MRI, CT, and prostate ultrasonography it might serve as an effective evaluation method during follow-up [29–31]. Therefore, this study will evaluate the feasibility of using PSMA PET/CT and its diagnostic accuracy to guide decision-making for cytoreduction in patients with newly diagnosed mHSPC treated with apalutamide and ADT.

This study will have a few limitations to be considered. First, this is a single-arm clinical trial without comparators. Therefore, the benefit of the treatment strategies in this study should be verified in further studies. Secondly, this is an exploratory trial with a relatively small sample size, and a firm conclusion cannot be drawn. Nevertheless, the findings of this study will provide preliminary evidence for a large randomized controlled clinical trial.

In conclusion, this study will provide a new clinical strategy, consisting of NHT and cytoreduction guided by PSMA PET/CT-guided in treating patients with newly diagnosed mHSPC and ≤ 10 metastatic sites. Further, the feasibility of the individualized therapeutic intervention developed in this study, including systemic therapy, cRP and MDT will be explored for managing patients with mHSPC. The findings of this study might provide evidence of the clinical management pathway, to further improve prognosis in patients with mHSPC.

## Data Availability

No datasets were generated or analysed during the current study.

## Abbreviations

ADT: Androgen deprivation therapy
CRF: Case report forms
cRP: Cytoreductive radical prostatectomy
EBRT: External beam radiotherapy
FAS: Full analysis set
GnRHa: Gonadotropin-releasing hormone analog
ICR: Independent central review
ITT: Intend-to-treat
MDT: Metastasis-directed therapy
mHSPC: Metastatic hormone-sensitive prostate cancer
MMT: Multi-modal therapy
MRI: Magnetic resonance imaging
NHT: Novel hormone therapy
OS: Overall survival
rPFS: Radiographic progression-free survival
SBRT: Stereotactic body radiation therapy
PET/CT: Positron emission tomography/computed tomography
PLND: Pelvic lymph node dissection
PSA: Prostate-specific antigen
PSMA: Prostate-specific membrane antigen
RECIST: Response Evaluation Criteria in Solid Tumours
TET: Total eradication therapy
TNM: Tumor-node-metastasis
